## Abstract

**Background:**

Risky sexual behaviors of adolescents in Mexico are a public health problem; 33.4 % of adolescent girls and 14.7 % of boys report not having used any protection at their first intercourse. The fertility rate is 77 births/1000 girls aged 15–19 years. The infrequent contact of adolescents with health services and the limited extent of school sex and reproductive health education require the support of innovative strategies. The objective of this paper is to present the design of an internet-based educational strategy to prevent risky sexual behaviors in Mexican adolescents.

**Methods:**

A field trial with intervention and comparison group and with ex-ante and ex-post measurements will be conducted in two public secondary schools. Adolescents between 14 and 15 years of age will participate. The intervention will be conducted in one school and the second school will serve as a comparison group where the investigators will observe the usual sex education provided by the school. The intervention will be delivered using an internet web page that includes four educational sessions provided during a 4 week period. Follow-up will last 3 months. Information on the study variables will be obtained through an Internet-based self-applied questionnaire and collected on three occasions: 1) when the adolescents enter the study (baseline), 2) once the intervention is completed (at 1 month) and 3) after 3 months of follow-up (at the fourth month). There will be three outcome variables: 1) knowledge in regard to sexually transmitted infections, 2) attitudes regarding condom use, and 3) self-efficacy toward consistent condom use. The generalized linear model will be used to assess changes in each outcome variable controlling for baseline measures and for study covariates.

**Discussion:**

The design and evaluation of an Internet-based educational strategy to prevent risky sexual behaviors in Mexican adolescents is important in order to provide a new, large-scale, easily implemented preventive tool.

**Trial registration:**

The study was registered at the ClinicalTrials.gov ID: NCT02686736.

## Background

Adolescence is a stage of life between 10 and 19 years of age in which young people experience complex biological, psychological and social changes. Some of these changes encompass rapid physical growth, sexual maturation, manifestation of sexual interest and initiation of sexual life [1] that usually begins between 15 and 19 years of age [2]. From a demographic perspective, adolescents represent a significant proportion of the population. In Latin America there are 148 million adolescents, accounting for 30 % of the total population [3].

Adolescents often engage in risky sexual behaviors that include unprotected sex, lack of contraceptive use, and multiple sexual partners. A recent multi-country survey representative of attitudes of young persons toward sex and contraception that included 5426 adolescents from 26 countries reported that, between 2009 and 2011, the number of young people having unprotected sex with a new partner increased substantially. For instance, in France, this increase was 111 % [4]. Furthermore, the proportion of adolescents with multiple sexual partners in the last 12 months increased to 41 % in developed countries and 58 % in developing countries [5].

These risky behaviors are associated with a high rate of unplanned pregnancies and sexually transmitted infections. According to the World Health Organization, 16 million girls aged between 15 and 19 years give birth every year with 95 % of these births occurring in “developing countries” [6]. Additionally, adolescents represent almost 50 % of new cases of sexually transmitted infections (STIs) [7]. Other important health consequences are unsafe abortions, pregnancy complications, infertility, significant psychosocial consequences and premature deaths [8].

In Mexico, risky sexual behaviors of adolescents are a public health problem. The 2012 Health and Nutrition National Survey (ENSANUT 2012 Spanish acronym) reported that 33.4 % of adolescent girls and 14.7 % of boys did not use any protection at the first intercourse [9]. Of sexually active female adolescents, 51.9 % had been pregnant; 5.7 % of adolescents from disadvantaged urban areas had herpes simplex virus, and 18 % had human papilloma virus [8]. The National Center for the Prevention and Control of Human Immunodeficiency Virus Infection (HIV) and Acquired Immune Deficiency Syndrome (AIDS) in Mexico has stressed that HIV is an important problem; ~180,000 Mexicans live with HIV. In 90 % of the cases, it was transmitted through sexual contact and in 94.1 % was due to inconsistent and incorrect condom use. In 2012, there were 9300 new cases registered of HIV infection; 5 % were adolescents [10]. Furthermore, ENSANUT 2012 reported that slightly more than half of Mexican adolescents had some knowledge about HIV transmission, symptoms and methods of prevention [11].

Previous research has highlighted the importance of early sex education and its association with a decrease in risky sexual behaviors rather than with earlier onset and higher frequency of sexual relations. However, adolescents have reported that their schools do not provide a comfortable environment for sex education [11, 12]. These findings justify developing effective educational strategies to prevent risky sexual behaviors able to reach large numbers of adolescents.

The educational and health sectors and mass media experts have drawn up and implemented strategies to prevent risky sexual behavior in adolescents [13–17]. Numerous research studies found that formal sex education is more likely to influence safe behavior if narrowly focused, has an explicit behavioral message, and develops negotiation skills [14, 15]. Most of these studies were conducted in high schools and results showed that participants reduced their risky sexual behaviors [16, 17]. However, these interventions were subject to limited school physical spaces, tight schedules and the need for trained personnel.

In Mexico, the health and educational sectors have been implementing strategies aimed at increasing the knowledge of adolescents about sexual and reproductive health issues. The health sector is offering preventive programs consisting of educational workshops in primary care facilities. The rate of use is low because only 53 % of adolescents affiliated with public institutions use such services [18] which, in turn, affect its potential impact. Also, the educational sector provides lectures and materials on sexual and reproductive health in different school grades. Sex education starts in the sixth grade of elementary school and continues through high school. However, the quality of the contents and delivery of these lectures is unknown, and previous figures regarding the percentages of unwanted pregnancies, unsafe sex, and prevalence of sexually transmitted infections among Mexican adolescents signal the need to improve the effectiveness of current strategies.

The literature review within the Mexican context identified a small number of school-based interventions [11, 19, 20]. These studies have shown a moderate positive effect of increasing the knowledge related to HIV and emergency contraception [11, 19] and with the intention to use condoms and contraceptives [19]. However, there are several restrictions to implement these strategies on a large scale through traditional educational techniques including lack of trained personnel and physical spaces, whereas the time assigned to this activity might be short.

Recently, a new line of research promoting sexual health through digital technology has emerged. Adolescents are frequent users of the Internet, mobile phones and video games and it is beneficial to take advantage of these tools to implement educational strategies to prevent risky sexual behaviors. A recent systematic review included ten studies on this subject, seven of which took place in the U.S. [21]. Two of these studies significantly delayed the initiation of sexual intercourse. Seven interventions significantly influenced psychosocial outcomes such as self-efficacy for abstinence and condom use. Six studies increased the knowledge of participants about HIV, sexually transmitted infections and contraception. This type of intervention has some advantages: 1) Accessibility from any computer connected to the Internet. 2) Ability to reach large numbers of people (i.e., scalability). 3) Flexibility for participants to access the intervention content at their convenience. 4) Capability to automate most aspects of the study (e.g., evolutional surveys). 5) Privacy for answering sensitive questions. 6) Affordability because the provision of these services to additional individuals represents low marginal costs. 7) Plasticity because it allows use of diverse visual materials [22].

In Mexico, the number of Internet users is on the rise. Between 2011 and 2012 the growth rate was 8.8 %, reaching 40.9 million persons. Adolescents are the most frequent users [23]. Internet-based educational interventions have proven to be feasible, flexible, and efficient and able to reach a large number of persons [21, 22]. However, this type of intervention is rare in developing countries such as Mexico.

An educational strategy provided through an internet portal could reach large numbers of Mexican adolescents and be able to increase their knowledge of sexual and reproductive health topics. Although this kind of intervention should be included within the school-based activities, it has the advantage that it does not require significant organizational changes regarding school schedules, physical space, or highly trained personnel. Therefore, the objective of this paper is to present the design of an internet-based educational strategy to prevent risky sexual behaviors in Mexican adolescents.

## Methods

A field trial of one intervention and one comparison group with ex-ante and ex-post measurements will be conducted in two public secondary schools in the Iztapalapa Delegation in Mexico City. A delegation represents a geo-political area; Mexico City is divided into 16 delegations. Compared to the rest of the delegations, Iztapalapa has less favorable socioeconomic indicators [24]. The intervention will take place in one school and the second school will serve as a comparison group where we will observe the usual sex education being offered. The schools will be selected through simple random sampling from the list of public secondary schools in Iztapalapa. The study population will consist of adolescents between 14 and 15 years of age who are in the third year of secondary school and agree to participate through informed consent. Parents are also required to sign written informed consent.

The project was authorized by the National Research and Ethics Committee of the Mexican Institute of Social Security (R-2014-785-033), the Research and Ethics Committee of the Hospital Infantil de Mexico Federico Gómez (HIM 2015-066) and the General Directorate of Technical Secondary Education of the Secretary of Education.

### Preparation of the intervention

The conceptual framework for the intervention and educational materials was based on the model of the Information-Motivation-and-Behavioral Skills proposed by Fisher and Fisher [25]. This model emphasizes that adequate information regarding risky sexual behavior, changing the motivational component and training in behavioral skills can influence initiation and maintenance of protective sexual behaviors.

A research group comprised of a pediatrician, psychologist, and sociologist designed the educational materials. All research team members have experience in educational interventions. The academic basis for developing the materials were the books “You, Your Life, Your Dreams” developed by International Family Care [1] and “Your Future in Freedom, for Responsible Sexuality and Reproductive Health” published by the government of the Federal District and the Secretary of Education of the Federal District of Mexico City [26]. Investigators also took into account the statistics on sexually transmitted diseases and adolescent pregnancies from the World Health Organization, ENSANUT 2012, the National Registry of AIDS cases, and information from the Planned Parenthood Federation of America.

We designed teen-friendly educational materials. To accomplish this, we used “avatars” from www.bitstrips.com, which are comics for teenagers. We created two central characters (a teenage boy and a teenage girl) who present the information in dialogue form and talk about their own experiences as well as the experience of their friends.

Two experts in the area of adolescent sexual and reproductive health reviewed the educational materials. Twenty adolescents between 14 and 15 years of age participated in three rounds of pilot testing. Both the teenagers and their parents agreed to participate in this phase through verbal informed consent.

We used the snowball sampling technique to choose the teenagers who participated in the pilot phase, which included ten boys and ten girls, with an average grade point of 8.5 (range 8.0–9.0). Their families were representative of different structures (nuclear, single-parent, extended), and their parents had varying levels of education. Most adolescents (18) had not initiated sexual activity and only two reported being sexually active. Experts and teens were asked if the educational information was clear, understandable and if it used appropriate language for teens or if it was contradictory, uncomfortable, or uninteresting. The teens were asked to evaluate whether or not they liked each educational session (using a scale from 1─3 where 1 = No, I do not like it, 2 = I like it more or less, 3 = I like it) and to explain why they disliked the educational information. The final version of the educational material was produced taking into account the comments and suggestions of experts and teens who rated the information highly. Although most adolescents who participated in the pilot testing had not initiated their sexual life, they reported that the information was clear and interesting.

### Description and evaluation of the intervention

The study materials are available on the Internet web page (http://tu-ssexual.com), which can be accessed with the participant e-mail address and a centrally assigned password.

The intervention will include an introduction and four educational sessions (Table 1) and will last 1 month (one session per week) followed by a 3-month follow-up. Teens will be allowed to access a weekly session at any time and as often as he/she likes. However, the sessions will be consecutive so teens will not be able to access to the subsequent session without completing the previous one. Each session has an average duration of 1 h and ends with overview questions. Additionally, at the end of each session, teens will be asked what they like and dislike about the session. Answers will be recorded in the study database.

**Table 1 Tab1:** Contents of the intervention

Session	Main topic	Contents
Introduction	Welcome	Welcome and general explanation of the organization of the website and instructions for its use.
		Invitation and compulsory automatic pass to answer the questionnaire that collects information on study variables.
1.	What I have to know before the first time or when it happened…?	1. What is dating? What is courtship? 2. Kisses, caresses and … what’s next? □ What is a sexual relationship? □ What is sexual pleasure? □ What is masturbation? □ What is sexual intercourse? □ Different sexual practices … 3. Having sex is the same for men as for women? 4. What should be a basis for a good relationship during courtship or dating? 5. How to recognize when your partner abuses you in order to not allow it (forms of abuse). 6. Self-esteem and its relation to self-care
2.	It is better to be informed and take care to prevent sexually transmitted infections	1. How sex can affect my health? Statistics of sexually transmitted infections (STIs) in adolescents in the world and in Mexico. 2. How can I realize when I or my partner has a sexually transmitted infection? 3. Are there medical tests to determine whether or not I have any type of sexually transmitted infection? 4. STIs affect women differently than men? 5. Are there vaccines to prevent STIs or treatments against them? 6. How I can protect myself from STIs? Ways to practice safe sex.
3.	It's better to know and care regarding HIV/AIDS and unwanted pregnancy.	1. HIV/AIDS: 1.1 How HIV/AIDS affects health. 1.2 Statistics on the prevalence of HIV/AIDS worldwide and in Mexico. 1.3. Ways of transmission of HIV/AIDS. 1.4 Common symptoms of people with HIV/AIDS: 1.5 Methods of detection and protection. 2. Is there any other risk in addition to STIs? And what if I get pregnant? What if my girlfriend gets pregnant? Teenage pregnancy statistics. Contraceptive methods: pros and cons. 3. Steps to use male and female condoms
4.	Preparing for a pleasant and safe sexual experience. Am I ready?	1. How can I negotiate condom use? Learning strategies for condom use negotiation 2. Tips for condom negotiation: □ at first intercourse □ at intercourse with a stable and casual partner □ when one of the two consumed alcohol □ when both are very excited 3. Make your own comics about how you would negotiate using a condom with your partner 4. E-sites on sexual and reproductive health

Furthermore, during the intervention and follow-up, booster e-mail messages will be sent to the teens of the intervention group. “Booster messages” will emphasize the main points of the educational sections and will be sent two to three times per week from the second week of the intervention.

Information on the study variables will be obtained through the Internet-based self-applied questionnaire and collected on three occasions: 1) when the adolescent enters into the study (baseline), 2) once the intervention is completed (at 1 month) and 3) after 3 months of follow-up (fourth month).

In the control group, teens will continue the usual school-provided sex education and will be invited to answer the Internet-based self-applied questionnaire at the same time as the intervention group. Furthermore, at the conclusion of the study, teens from the control group will also receive access to the educational sessions.

### Recruitment and retention strategies

To improve recruitment and retention of teens in the study, we will implement strategies focused on teens, their teachers and parents. Recruitment strategies will incorporate provision of information and reinforcement of the potential benefits of the intervention. Retention strategies will include the following: 1) e-mail reminders of each session; 2) placing reminders with brief thematic description of the weekly session in classrooms; 3) follow-up e-mail messages about technical and other problems regarding each learning session and solutions to such problems; 4) parent and teacher involvement in motivating adolescents’ participation.

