Also, several limitations can be noted. (i) The proposed study design is ‘quasi-experimental’ with one intervention and one comparison group, with ex-ante and ex-post measurements. Therefore, the assignment of teens to the intervention and control groups will not be random. This could lead to interpretation problems if baseline measurements differ between groups. Furthermore, in order to address baseline differences between intervention and control group we proposed to perform the D-in-D estimator in the framework of a generalized linear regression model. (2) Due to financial feasibility issues we could not use an extensive (6 months or longer) follow-up and evaluate health-related outcomes such as pregnancies and sexually transmitted infections.

In conclusion, it is justifiable to design and evaluate an Internet-based educational strategy to prevent risky sexual behaviors in Mexican adolescents in order to provide a new, large scale, easily implemented and preventive tool.

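### Recruitment stresses the intervention's benefits, each arm is one school, and no step conceals the arm until consent and baseline are done: if the arm is known, volunteers can differ by school in ways the analysis cannot remove

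*Protocol article*

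**What the plan says.** **Allocation.** Under Methods, chance enters at one point only: "The schools will be selected through simple random sampling from the list of public secondary schools in Iztapalapa". One of the two sampled schools then receives the website and the other continues usual sex education. How the intervention school is chosen is not described. On teens, the Discussion is explicit: "Therefore, the assignment of teens to the intervention and control groups will not be random".

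**Entry.** Methods defines the participants as 14- to 15-year-olds "who are in the third year of secondary school and agree to participate through informed consent", and parents must also consent in writing. Each school's sample is therefore a sample of volunteers.

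**Recruitment message.** Recruitment and retention strategies are aimed at teens, teachers and parents: "Recruitment strategies will incorporate provision of information and reinforcement of the potential benefits of the intervention". No arm-specific wording is given, and no wording common to both schools.

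**Timing of the benefit.** The intervention school gets the sessions during the trial. For controls, "at the conclusion of the study, teens from the control group will also receive access to the educational sessions".

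**Baseline.** In Table 1 the website Introduction contains "Invitation and compulsory automatic pass to answer the questionnaire that collects information on study variables". Controls are invited to answer the questionnaire at the same times.

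**Safeguards.** Study variables and Statistical analysis plan a differences-in-differences (D-in-D) estimator and a generalized linear model (GLM) adjusted for baseline measures and listed covariates. The limitations in the Discussion say of the non-random assignment: "This could lead to interpretation problems if baseline measurements differ between groups".

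**The concern.** With one school per arm, anyone who knows the school's arm knows the teen's arm. A teen or parent in the intervention school would then be weighing immediate access. One in the comparison school would be weighing repeated questionnaires now and access later. The teens who say yes to these two propositions need not be alike, and the relevant difference is interest in the subject. A motivated teen is likely to gain more in knowledge, attitudes and self-efficacy over four months, whatever the starting score.

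Such a difference affects the change itself, and the between-group difference in change is the effect estimate. The stated limitation is conditional on baseline measurements differing. Two volunteer groups can match at baseline and still be expected to change differently.

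The direction cannot be foreseen. An attractive immediate offer may draw the keenest teens into the intervention arm and inflate the effect. Alternatively, only the keenest may accept a delayed benefit in the comparison school, which would hide an effect. The problem arises at entry, so it is distinct from drop-out and from fixed differences between the schools.

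**Working it through.** The article gives no consent rate and no measure of motivation, so it has no figure of its own to reproduce on this point. The calculation shows what range of bias is plausible; it does not estimate this trial's bias.

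**Step 1. What the planned analysis removes.** Write a teen's expected change as *c + g·Z*, where *Z* is motivation in SD units and *g* is the change, in SDs of change, per SD of *Z*. With no true effect, D-in-D estimates *g × (mean Z among intervention volunteers − mean Z among control volunteers)*. A constant gap in scores cancels; this term does not. Covariate adjustment removes the part of *Z* that the covariates predict. The listed covariates are parental education, occupation, family structure and communication; media information; sex, age, grades, substance use and social desirability. None measures interest in the topic or in the study directly. Grades, communication and baseline scores are partial proxies.

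**Step 2. Inputs.**
- From Sample size: 200 per group and 25% drop-out, so 200 × 0.75 = 150 completers per group.
- Standard error of a difference in mean change, in SDs of change and treating teens as independent: √(2/150) = 0.1155.
- Assumed: the same share of teens joins in both schools (50%, 70% or 85%). The log-odds of joining rise by *b* per SD of *Z* in one school (0.5 or 1.0) and do not depend on *Z* in the other. *g* is 0.2 or 0.4. There is no true effect and no covariate adjustment.

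**Step 3. Results.** Bias = *g* × difference in mean *Z*. False-positive rate = Φ(bias/0.1155 − 1.96) + Φ(−bias/0.1155 − 1.96).

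| *b* | Share joining | Difference in mean *Z* | Bias, *g* = 0.2 | Bias, *g* = 0.4 | False-positive rate, *g* = 0.4 |
|---|---|---|---|---|---|
| 0.5 | 85% | 0.073 | 0.015 | 0.029 | 5.7% |
| 0.5 | 70% | 0.143 | 0.029 | 0.057 | 7.8% |
| 0.5 | 50% | 0.236 | 0.047 | 0.094 | 12.9% |
| 1.0 | 85% | 0.133 | 0.027 | 0.053 | 7.5% |
| 1.0 | 70% | 0.253 | 0.051 | 0.101 | 14.1% |
| 1.0 | 50% | 0.413 | 0.083 | 0.165 | 29.8% |

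Worked example, last row: 0.4 × 0.413 = 0.165; 0.165/0.1155 = 1.43; Φ(−0.53) + Φ(−3.39) ≈ 0.298. At the mildest corner (bias 0.015) the rate is 5.2%.

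**Step 4. Direction and the null case.** If the school with selection is the intervention school, the bias favours the website. If it is the comparison school, the sign reverses. If joining depends on *Z* equally in both schools and the same share joins, the difference in mean *Z* is zero and so is the bias.

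**The case against.** The strongest reply is that the article never gives the order of allocation, disclosure and consent. It describes one set of recruitment strategies for all teens, and controls do receive the sessions eventually, so the benefits can be presented truthfully in both schools. Script and sequence may well be in the full protocol. This stands: a reader might infer that every teen's arm was openly known at recruitment, or that the two schools were given different offers, and neither is stated. What remains is a stated non-random assignment by school, a stated benefit-led message, a stated difference in when the benefit arrives, and a limitation that covers only differing baselines.

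A reader might also take the placing of the questionnaire within the website Introduction as proof that enrolment was unconcealed or baseline contaminated. The text does not support this. The pass comes before session 1, the site needs a centrally assigned password, so a teen has probably already enrolled, and the article does not say that controls use a different page.

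Nor is D-in-D the only safeguard. The GLM adjusts for baseline and for covariates that partly track interest, so the biases tabulated without adjustment lean high.

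Finally, a harsher model, in which consent is decided wholly by a cut-off on motivation, gives larger figures. With 90% consent in one school, 50% in the other and a correlation of 0.4, the bias is 0.4 × (0.798 − 0.195) = 0.24 SD and the false-positive rate 55%. That should not be used as the headline. Nothing supports so strict a selection, and in that model the lower-consent school holds the keener teens. If controls consented less, most of those false positives would favour control.

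**Conclusion.** The point holds in conditional form. If the arm is known when teens and parents are approached, the volunteers can differ by school, and the planned analysis does not remove selection on an unmeasured trait that drives change. The premise is a reasonable inference from one school per arm and the absence of any described concealment, but it remains an inference.

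Size and direction are unknown. Under the assumed inputs the bias runs from negligible (0.015 SD) to roughly 0.15 SD (0.165 at the extreme), with false-positive rates of about 5% to 30%. These figures rest on the assumed joining model, on 150 independent completers per group, and on no help from covariates. The bias is zero if offer and consent process are the same in both schools.

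The admission that the design is quasi-experimental does not dispose of the point, because it addresses differing baselines and not who volunteers. The matter is worth correcting because the remedy is cheap and no later analysis can restore concealment.

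**What to change.** In Methods, Description and evaluation of the intervention, and Recruitment and retention strategies, state this order:

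1. Sample the two schools, as planned.
2. Recruit teens, parents and teachers in both with one identical message and consent form, for example 'access to the sessions now or after the study ends'. This is truthful, since controls are already promised the sessions.
3. Complete consent and the baseline questionnaire in both schools on the same page, before any session opens.
4. Then draw by lot which school starts now, and disclose it.
5. Report the numbers eligible, consenting and completing baseline in each school.

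In the Discussion, add differential volunteering as a limitation, and state that a draw between two schools does not remove school-level confounding.

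The cost is a change of wording, one draw, and a short delay, because sessions open only once both schools have finished baseline. The message may be slightly less attractive. No extra participants are needed, and the questionnaire is already online.

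If the arms are already disclosed, use the common message for any remaining recruitment, report the counts by school and state the limitation.
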